**Fig. 2 Fig2:**
[figure not shown]
Standard Protocol Items: Recommendations for Interventional Trials (SPIRIT 2013) diagram illustrating the schedule of enrolment, post allocation, and close-out for all assessments. CC cognitive control, CI cognitive intervention, EC exercise control, EI exercise intervention, ERP event-related potential, LSI Life Satisfaction Index, 6MWT 6-Minute Walk Test, PANAS Positive and Negative Affect Schedule, SPPB Short Physical Performance Battery, TMT Trail Making Test, WMS-III Wechsler Memory Scale—Third Edition

To report the primary and secondary outcomes, we will follow the outcome definition proposed by Saldanha et al. [85] and Zarin et al. [86] that includes the domain, the specific measurement, the specific metric, the method of aggregation, and the time points that will be used for analysis.

### Primary outcomes: training effects on cognitive functions

#### Set-shifting

##### Memory-based task switching

Executive functions will be assessed with a memory-based task-switching paradigm. In this task [76, 87], digits from 1 to 9 (excluding number 5) are presented in white on a black background on the computer screen. A cue indicating the relevant task is presented simultaneously with the digit below the fixation point. The cue “NUM” indicates a numerical task (smaller or greater than 5), “PAR” the parity task (odd vs. even), and “TAM” (a diminutive for Spanish “tamaño” (size) font) the font-size task (small vs*.* large). Each stimulus is presented in small (7 mm × 10 mm) and large (12 mm × 18 mm) size. Participants will perform three single and two mixed blocks. In the single blocks, they have to process digits according to the one-task rule (i.e., numerical, parity, or font-size task only). In the memory-based mixed blocks, participants have to switch between different tasks within the block. In the cue block they are instructed to switch the rule after every three trials in the following order “NUM–NUM–NUM–PAR–PAR–PAR–TAM–TAM–TAM”, while a cue is presented in every trial simultaneously with the digit. In the memory block, participants are instructed to switch the rule after every three trials in the same order, while “XXX” instead of a cue is presented; that is, participants have to keep track of the trial sequence in their working memory. When three consecutive errors are made, or no response is given, cues are presented on three consecutive trials to help participants to find the track. Single blocks consist of 35 trials each, and two mixed blocks consisting of switch and no-switch trials: a cued block (90 trials) and a memory block (90 trials). The mixed blocks are equal with respect to the stimulus type, response type, and frequency of task switch (33.3%). The stimulus–response mapping of the three tasks is overlapping; that is, responses according to “smaller than 5”, “even”, and “small size” are assigned to the left key and “larger than 5”, “odd”, and “large size” to the right key. The assignment will be counterbalanced across participants. The outcomes of interest are mean reaction times (RTs) between groups corresponding to correct trials at pretest, posttest, and follow-up time points. The specific metric will be the change from baseline.

#### Processing speed and flexibility

##### Trail Making Test (TMT)

The TMT is a neuropsychological test of visual attention and task switching. The test comprises two parts (A and B). Each part consists of 25 circles distributed over a sheet of paper. In Part A, the circles are numbered 1–25, and the participant draws lines to connect the numbers in ascending order. In Part B, the circles include both numbers (1–13) and letters (A–L); the task consists of connecting the circles in an ascending pattern, but with the added task of alternating between the numbers and letters (i.e., 1–A–2–B–3–C, etc.). The total times in seconds for Parts A and B represent the TMT-A and TMT-B direct scores. Scores of TMT-A account for perceptual speed, whereas the B–A difference score is an indicator of task-switching abilities. The outcomes of interest are the mean time scores of the difference score, TMT-B minus TMT-A, to assess task switching between groups at pretest, posttest, and follow-up time points. The specific metric will be the change from baseline.

#### Working memory

The *N*-back task is a continuous performance task to assess maintenance and updating of information in working memory. This task has been used with older adults [88–90]. Participants are presented with a sequence of stimuli (consonant letters), and indicate whether the last stimulus matches the one presented “*n*” trials back by pressing one of two keys (one for “yes” or another for “no”). We used a three level *N*-back task. In the 0-back condition, the letter X is the target. We include the 0-back condition as an index of perceptual-motor speed to control for the role of speed of processing in working memory performance. In the 1-back condition, participants have to remember the stimulus presented just before the current stimulus; in the 2-back level, they have to remember the stimulus presented two positions before. Each participant first performs a practice block of 17 trials at each level, followed by the experimental trials. Each level contains three blocks of 27 trials (81 trials per level), yielding a total of 243 trials. Each block of 27 trials consists of 17 “nontargets” (“no” response) and 10 “targets” (“yes” response). The outcomes of interest are the mean accuracy between groups as assessed by Hits–False alarms. The specific metric will be the change from baseline (pretest) to posttest and follow-up.

#### Inhibitory control

The Stroop interference effect reflects the extra time needed to resolve the conflict generated by an automatically processed irrelevant dimension. The Stroop task assesses response inhibition. We use the computerized Color–Word version of the Stroop task [42] with two different conditions: in the congruent condition, color name words match with the ink color; while in the incongruent condition, color names are printed in an incompatible ink color. In both conditions, participants are instructed to name the color of the ink as soon as possible. Longer response latencies and higher error rates on incongruent trials (when the color of the letters conflicts with the word) compared to congruent trials (when color and word match) constitute the Stroop effect. The Stroop effect correlates negatively with the efficiency of inhibitory control. The Stroop task contains 18 practice trials and two experimental blocks of 126 trials each, with a proportion of incongruent trials of 66%. Responses are assigned to the keys “v”, “b” and “n”, and the stimulus–response mapping is counterbalanced across participants. The dependent variable is the mean RT corresponding to the congruent and incongruent correct trials of the groups at pretest, posttest, and follow-up. The specific metric will be the change from pretest in the computerized version of the Stroop task to assess response inhibition.

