#### Cognitive intervention

In each session, participants in the CI group will play 10 video games selected from the commercial Lumosity computerized training program (http://lumosity.com/). Lumosity provides a series of games targeting the improvement of several cognitive functions. Table 1 presents a short description of the games and their trained domains. These functions are sensitive to age-related cognitive decline and closely related to the ability to perform activities of daily living, such as driving. The participant will play the games in a predetermined sequence, for approximately 5–10 min for each game. Each participant in the CI group will have a Lumosity user account assigned. These games are adaptive—meaning that as performance improves, the difficulty increases, progressively adjusting to the participant’s performance level.

**Table 1 Tab1:** Short description of the video games for the cognitive intervention

Game name	Trained function	Description
Train of Thought	Divided attention	The player directs trains to their matching station
Assist Ants	Divided attention	The player prevents collisions by placing obstacles in their paths
Trouble Brewing	Divided attention	The player simultaneously serves orders to different customers
Playing Koi	Divided attention	The player keeps track of which fish has already been fed, in a square of randomly appearing fishes
Memory Serves	Working memory and divided attention	The player matches different pieces of luggage to their corresponding owners
Disillusion	Flexibility	The game consists of matching tiles with different shapes, colors, or symbols
Ebb and Flow	Flexibility	The player swipes in the direction to which the leaves are moving or pointing
Master Piece	Spatial reasoning	The player reorientates a shape so that it fills a hollow section
Speed Pack	Visualization	The player has to fit the last item into an already filled suitcase
Highway Hazards	Information processing	The player dodges obstacles in a race through a virtual desert

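### Stroop and task switching are scored on correct-trial reaction time alone, so no stated outcome would reveal a speed gain bought with more errors

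*Protocol article*

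**What the plan says.** All statements are in the protocol article.

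- **Inhibitory control (Stroop), construct.** The section opens in terms of time: "The Stroop interference effect reflects the extra time needed to resolve the conflict generated by an automatically processed irrelevant dimension". It then adds a second component, saying that "Longer response latencies and higher error rates on incongruent trials" than on congruent ones make up the effect. It gives the direction of interpretation: "The Stroop effect correlates negatively with the efficiency of inhibitory control".
- **Inhibitory control, scoring.** "The dependent variable is the mean RT corresponding to the congruent and incongruent correct trials of the groups at pretest, posttest, and follow-up". The metric is change from pretest. The only response instruction stated concerns speed: "participants are instructed to name the color of the ink as soon as possible".
- **Memory-based task switching, scoring.** "The outcomes of interest are mean reaction times (RTs) between groups corresponding to correct trials at pretest, posttest, and follow-up time points". The metric is change from baseline. Errors are used only to bring back the cues after three in a row.
- **Other primary outcomes.** N-back, Faces and Word-Pair List are scored as hits minus false alarms, so accuracy is a named outcome elsewhere.
- **Statistical analysis.** Four groups by three time points in a repeated-measures ANOVA, with Bonferroni-corrected post hoc tests. No error-rate or joint speed-accuracy analysis is named for these two tasks.

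**The concern.** RT in a choice task depends on ability and on how much evidence a person waits for before responding. Someone who becomes less cautious responds sooner and makes more errors. If errors are discarded and only the remaining RTs are scored, that change looks like improvement. Two primary executive outcomes are scored this way, and one of them is described in the same section as having an error component.

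Randomization does not remove the problem if the change in caution is itself produced by training. That is plausible here. The cognitive intervention uses games such as dodging obstacles and serving several customers at once, and "These games are adaptive—meaning that as performance improves, the difficulty increases, progressively adjusting to the participant’s performance level". The control games are word and general-knowledge games. The reverse can also happen: an arm that becomes slower but more accurate would be scored as worse.

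Data analysis is stated to be unblinded (Randomization and blinding). A decision made after the results are known on whether and how to bring in errors would therefore be hard to defend.

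**Working it through.** **1. Is this a fixed rule or an omitted detail?** The Outcome measures section says each outcome is given by domain, measurement, metric, aggregation and time points. The two task sections fill in those items with correct-trial RT, while three other primary outcomes are given accuracy scores. So the RT-only rule is positively stated.

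**2. Trials.** Stroop has "two experimental blocks of 126 trials each, with a proportion of incongruent trials of 66" percent: 2 × 126 = 252 trials, of which 252 × 0.66 ≈ 166 are incongruent and about 86 congruent. Error rates can be computed by condition from trials already run.

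**3. Can both forms of RT score improve with no gain in ability?** The document gives no RT or accuracy figures, so this uses an assumed model: the two-choice diffusion model with unbiased start and unit noise, drift *v* (ability), boundary *a* (caution) and fixed non-decision time *t*.

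- Accuracy = 1 / (1 + e^(−av))
- Mean RT = *t* + (a / 2v) × (1 − e^(−av)) / (1 + e^(−av)). In this model it is the same for correct and error trials.

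Incongruent trials with *v* = 1.8 and *t* = 400 ms:

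- *a* = 2.0: av = 3.6 and e^(−3.6) = 0.0273. Accuracy = 0.973. RT = 400 + 1000 × 0.5556 × 0.9468 = 926 ms.
- *a* = 1.2: av = 2.16 and e^(−2.16) = 0.1153. Accuracy = 0.897. RT = 400 + 1000 × 0.3333 × 0.7932 = 664 ms.

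Three assumed settings, with only *a* changing within each:

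| Drift cong. / incong.; *t* | *a* | RT cong. (ms) | RT incong. (ms) | RT interference (ms) | Error cong. / incong. (%) | Error effect (points) |
|---|---|---|---|---|---|---|
| 2.5 / 1.8; 400 ms | 2.0 → 1.2 | 795 → 617 | 926 → 664 | 131 → 47 | 0.7 / 2.7 → 4.7 / 10.3 | 2.0 → 5.6 |
| 3.0 / 2.0; 400 ms | 2.0 → 1.2 | 732 → 589 | 882 → 650 | 150 → 61 | 0.2 / 1.8 → 2.7 / 8.3 | 1.6 → 5.7 |
| 2.2 / 1.5; 450 ms | 1.6 → 1.4 | 793 → 740 | 895 → 815 | 102 → 75 | 2.9 / 8.3 → 4.4 / 10.9 | 5.4 → 6.5 |

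In every row raw RT and RT interference both fall, while the error effect rises. Scoring incongruent minus congruent RT therefore does not remove the problem.

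**4. Does a rate score settle it?** Correct responses per second in the first row: congruent 0.993 / 0.795 = 1.25 → 0.953 / 0.617 = 1.54; incongruent 0.973 / 0.926 = 1.05 → 0.897 / 0.664 = 1.35. This score also rises with ability fixed, so a combined score can only support the error rate, not replace it.

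**5. Can a false-positive rate be attached?** Take the third row, assume the whole shift occurs in one of two arms of 36, and assume an SD of change of 100 to 150 ms. The noncentrality is shift / (SD × √(2/36)) on 70 degrees of freedom.

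- Raw RT, pooled over trials: the shift is about 70 ms. A two-sided 5% test rejects in 83% to 50% of trials, or 60% to 24% at 0.05/6 (six pairs assumed).
- RT interference: the shift is 102 − 75 = 27 ms. It rejects in 20% to 12%, or 6% to 3% at 0.05/6. If a difference score had an SD of 50 ms, the 5% figure would be 62%.

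The result runs from negligible to very large depending on the assumptions, so no single figure is supported.

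**The case against.** **The Stroop section opens with time, and one component of an effect may be chosen as the outcome.** This is fair. The section is mixed rather than flatly contradictory, and RT alone is a possible choice. But smaller RT interference is to be read as better inhibition, and that reading is unsafe without the error component.

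**A reader might infer the same contradiction for task switching.** The document does not support that, since it gives no latency-and-error definition there. Only the scoring gap stands.

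**A reader might infer that errors will never be analysed.** The article does not say so. Naming RT does not exclude supporting analyses, and the full plan is not shown. What stands is that the stated outcome rule leaves errors out.

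**A reader might infer that the cognitive-intervention arms will become less cautious.** This is not established. Nothing says whether the control games are timed, or that the training games reward speed over accuracy. Bias arises only if caution changes unequally between arms. The multidomain and cognitive-only arms both receive the cognitive intervention, so this mechanism gives no reason to expect a false advantage of one over the other.

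**Model and safeguards.** Stroop uses three keys and the model has two choices, so it shows possibility, not likelihood. N-back is scored on accuracy, and re-cueing limits long runs of errors. Neither detects a change in caution on these two tasks.

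**Conclusion.** The point holds as a weakness in outcome definition. For Stroop, the scored outcome leaves out half of the effect as the section itself describes it. For task switching, errors are simply unscored. As written, a change in response caution in one arm would improve raw RT and RT interference with no better inhibition or shifting, and no stated outcome would show it.

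The direction follows from any model in which faster responding can be bought with errors. The amounts in the working rest on assumed drift, boundary, non-decision time and SD. A differential shift between arms is a plausible risk, not a finding, and its size cannot be derived from the document. It is worth correcting because correction is cheap and the two outcomes are primary.

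**What to change.** In the Memory-based task switching and Inhibitory control sections:

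1. Name error rate as a companion outcome to RT, for the same trial types: incongruent versus congruent for Stroop; switch, no-switch and single for task switching.
2. Analyse it with the same group-by-time model as RT.
3. State that RT gains will be interpreted jointly with the estimated between-group difference in error change and its confidence interval. A bare rule that any rise in errors cancels an RT gain should be avoided: with no margin or test, a chance rise could veto a real effect.
4. Where RT and errors move in opposite directions, add a combined speed-accuracy score as a supportive sensitivity analysis only, since a simple rate score can also rise when only caution falls.

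**Cost.** No new data, a few lines of text and one more model per task. An RT gain accompanied by more errors could no longer be claimed outright as improved executive control.

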##### Wechsler Memory Scale—Third Edition (WMS–III) Word-Pair List

The WMS-III Word-Pair subtest assesses immediate and delayed verbal memory. In this test, four trials of eight unrelated word pairs are presented at a rate of 3 s per pair. In the immediate recall condition, after the presentation of the four lists, the first word of each pair is read to the participant, who has to provide the associated word of the pair. After a delay of approximately 25–35 min, the same procedure is repeated, and the participant provides the second word of each pair. Finally, a recognition task is administered where 24 word pairs are presented and the participant is asked to identify the pair as either “new” or “old”. The Hits–False alarms mean between groups at pretest, posttest, and follow-up assessments will be the outcome of interest. The specific metric will be the change from pretest to posttest and follow-up.

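### Three primary cognitive outcomes are defined by scores that do not isolate, do not clearly name, or only partly cover the function they stand for (task switching, Stroop, word pairs)

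*Protocol article*

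**What the plan says.** All three outcomes stand under the heading for primary outcomes in the protocol article.

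- **Task switching (set-shifting).** The task has three single blocks, a cued mixed block and a memory mixed block, and the mixed blocks contain switch and no-switch trials. The outcome is: "The outcomes of interest are mean reaction times (RTs) between groups corresponding to correct trials at pretest, posttest, and follow-up time points". The metric is change from baseline. No switch cost or mixing cost is named.
- **Stroop (Inhibitory control).** The section describes interference as added time on conflict trials, defines the Stroop effect by comparing incongruent with congruent trials, and relates that effect to inhibitory efficiency. It then fixes the outcome: "The dependent variable is the mean RT corresponding to the congruent and incongruent correct trials of the groups at pretest, posttest, and follow-up". The metric is change from pretest.
- **WMS-III Word-Pair List.** The test has immediate cued recall, delayed cued recall and, last, an old/new judgement on 24 pairs. The only score is: "The Hits–False alarms mean between groups at pretest, posttest, and follow-up assessments will be the outcome of interest".
- **Trail Making Test, for comparison.** Here the protocol separates speed from switching: "Scores of TMT-A account for perceptual speed, whereas the B–A difference score is an indicator of task-switching abilities". It makes the difference score the outcome.
- **Statistical analysis.** The primary model is a repeated-measures ANOVA with four groups and three time points. No within-task factor is named.

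**The concern.** The main objective names set-shifting, response inhibition, and immediate and delayed verbal memory. Each needs a score that responds to that function.

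Mean RT in a switching task responds to anything that makes a participant faster. The Background reports that computer-based training in older adults affects processing speed, among other functions. The cognitive-intervention games are adaptive and one is listed as training information processing, whereas the control games train lexical access, semantics and general knowledge. A difference between arms in general speed is therefore plausible on the protocol's own account. Under the stated outcome it would be reported as better set-shifting. The same would hold for inhibition if Stroop RT is pooled over conditions.

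For word pairs the risk runs the other way: a benefit in recall would not be seen, because the stated score cannot be formed in the recall phases.

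The section on randomization and blinding says that data analysis will not be blinded. That makes it more important to fix the choice between raw RT and a cost score before results are seen.

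**Working it through.** The plan gives no figure to reproduce on this point. The check uses the protocol's trial counts and a comparison of its sections.

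**Task switching**

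Inputs (section on memory-based task switching): 35 trials in each of three single blocks, 90 trials in each of two mixed blocks, and a switch frequency of 33.3% in the mixed blocks.

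- Single trials: 3 × 35 = 105. Mixed trials: 2 × 90 = 180. Total: 105 + 180 = 285.
- Switch trials: 180 / 3 = about 60. No-switch trials: about 120.
- Weight *w* of switch trials in mean RT: 60 / 285 = 0.21 over all blocks, or 60 / 180 = 0.33 over mixed blocks only. The protocol does not say which blocks enter the mean.

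With all trials correct and the other trial types unchanged, a change *d* in switch cost moves mean RT by *w* × *d*. A uniform speed change *s* moves mean RT by *s* and leaves switch cost unchanged. The documents give no expected effect in milliseconds, so the values of *d* below are assumptions.

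| Assumed fall in switch cost | Mean RT, all blocks | Mean RT, mixed blocks | Switch minus no-switch |
|---|---|---|---|
| 30 ms | 30 × 0.21 = 6 ms | 30 × 0.33 = 10 ms | 30 ms |
| 60 ms | 60 × 0.21 = 13 ms | 60 × 0.33 = 20 ms | 60 ms |

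A uniform speed-up of 6–20 ms, with no change in switching, gives the same movement in mean RT.

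**Stroop, only if RT is pooled over conditions**

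Inputs (section on inhibitory control): two blocks of 126 trials, 66% incongruent.

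- Trials: 2 × 126 = 252. Incongruent: 252 × 0.66 = about 166. Congruent: about 86.
- Pooled mean RT = congruent RT + 0.66 × interference.
- An assumed 30–60 ms fall in interference moves pooled RT by 30 × 0.66 = 20 ms to 60 × 0.66 = 40 ms. A uniform 20–40 ms speed-up does the same with inhibition unchanged.
- If RT is kept by condition and the difference is analysed, none of this applies.

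**Word pairs: phases against the stated score**

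| Phase | Task as described | Foils present | Hits–False alarms available |
|---|---|---|---|
| Immediate | Participant supplies the paired word | No | No |
| Delayed recall | Participant supplies the paired word | No | No |
| Recognition, after the delay | 24 pairs judged old or new | Yes | Yes |

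The Faces subtest has essentially the same outcome wording. There both phases are recognition with distractors, so the score works for immediate and delayed memory. It does not carry over to the recall phases of the word-pair test.

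**The case against.** The best case against the point is that a journal article condenses. One generic group-by-time design is given for every outcome, and the N-back shows the same brevity: it has three levels, includes the 0-back level to control for speed, and still states only mean accuracy. Silence on within-task factors therefore does not rule them out, and a full analysis plan may supply them. This stands as far as it goes: the missing factor alone would not be a fault. But the article says that it will define domain, measurement, metric and aggregation for each outcome, and it then states the metrics questioned here.

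Several stronger readings are tempting, and the documents do not support them:

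- *The Stroop outcome is certainly a pooled raw mean.* The sentence names both conditions, and the section says that the measure is meant to assess response inhibition. RT kept by condition is a fair reading. The fault is ambiguity.
- *Hits–False alarms is invalid for the word-pair test.* It is valid for the recognition task and incomplete for the test as a whole.
- *Set-shifting is not measured in this trial.* The Trail Making difference score is also a primary outcome and is meant to assess task switching. ERPs are recorded during the switching task as well.
- *Speed practice is peculiar to the cognitive-intervention arms.* Cognitive intervention and control activity both run on tablets, and the intervention games are described as adaptive, not as timed. Differential speeding is plausible but not shown.

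It is also fair to say that switch cost is not the only sensible contrast, since the block structure supports a mixing cost too.

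**Conclusion.** The point holds, with a different strength for each outcome.

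- **Task switching: clear.** The stated outcome does not isolate set-shifting. A change in switch cost appears in mean RT at 21–33% of its size, while general speed appears at full size. The weights rest on the protocol's counts, on all trials being correct, and on either all blocks or mixed blocks entering the mean. The 6–20 ms illustration also rests on the assumed 30–60 ms.
- **Stroop: ambiguous.** The section ties inhibition to a difference between conditions, and the outcome sentence does not state that difference. If RT is pooled, the fault is the same as for task switching. If it is kept by condition and contrasted, there is no fault.
- **Word pairs: incomplete.** Immediate and delayed cued recall have no usable score, so immediate verbal memory, which the objective names, has no defined word-pair outcome.

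The three definitions should be settled before the outcome data are analysed.

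**What to change.** Reword the three outcome definitions and align the model with them.

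- **Task switching:** define the set-shifting outcome as switch minus no-switch RT on correct trials in the mixed blocks. A mixing cost (mixed minus single blocks) may be added. Equivalently, add trial type to the model and test group × time × trial type.
- **Stroop:** define the outcome as incongruent minus congruent RT on correct trials, or add congruency and test group × time × congruency.
- **Word pairs:** score the number of words correctly recalled, with immediate and delayed recall kept separate, and report recognition Hits–False alarms as its own measure. The recall score should follow the test as actually administered. The article describes recall after the four lists have been presented, so a sum over four recall trials cannot be assumed from it.
- **Raw RT:** it may be kept, labelled as a processing-speed measure.

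The tasks as described already yield the data, and the sample-size calculation does not depend on these definitions. The cost is precision: RT difference scores are noisier than raw means, a price the protocol already pays for the Trail Making Test. Scoring recall and recognition separately also adds measures, so the text should say which of them are primary.
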